#### Methods for additional analyses (e.g., subgroup analyses) 20b

No subgroup analyses are planned.

#### Methods in analysis to handle protocol non-adherence and any statistical methods to handle missing data {20c}

The analysis will follow an ITT approach, which will include the data from the excluded patients in the results. The reason for each patient’s withdrawal, especially the occurrence of any side effects, will be explained in detail. Missing data will be addressed by multiple imputations.

#### Plans to give access to the full protocol, participant-level data, and statistical code {31c}

The corresponding author will provide the dataset if there are any logical requests for data in line with the present protocol. Otherwise, all information will be kept confidential.

### Oversight and monitoring

#### Composition of the coordinating center and trial steering committee {5d}

The researchers and all aspects of the study will be supervised by the Ethics Committee and the Vice-Chancellor of Isfahan University of Medical Sciences, who will ensure that the study adheres to ethical principles and protects the patient’s health and dignity. In case of any ethical violations, the study may be corrected or terminated. The principal investigator is the lead researcher and main coordinator of the trial. The principal investigator and research physician are in charge of recruiting, treating, and following up with participants. A steering committee will oversee the entire study process. The study team will also communicate regularly to monitor progress.

### Composition of the data monitoring committee, its role, and reporting structure {21a}

The academic committee of Isfahan University of Medical Sciences will conduct impartial and continuous data monitoring.

### Adverse event reporting and harms {22}

According to previous studies, supplementation with inulin at a dosage of 10 g per day has been found to be safe and devoid of serious side effects [39, 40]. In the event of any complications arising from inulin supplementation, the intervention will be promptly discontinued, and the necessary medical measures will be taken. Any potential adverse effects will be reported to the Ethical Committee of Isfahan University of Medical Sciences. Based on the severity and nature of the adverse effects associated with supplementation, the ethical committee will determine whether to exclude the patient from the study or assign an exclusive code or undertake other appropriate actions.

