### Reason for eliminating the data

Consumption of less than 80% of inulin supplements by the patient.

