#### Criteria for discontinuing or modifying allocated interventions {11b}

Patients may withdraw from the trial at any time for any reason. The investigator may withdraw patients from the trial to protect their safety or if they are unable or unwilling to continue with the trial. Furthermore, the reasons for each patient’s withdrawal from the trial will be explained in detail in the study results.

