#### Strategies to improve adherence to interventions {11c}

Patients will be provided with inulin and placebo packs at weeks 1, 4, and 8. At the baseline, each phone call, and intermediate visits, all patients will receive instructions on how to use their supplements. They will be requested to return the packs with any remaining contents at the end of each 4-week period, and any side effects experienced will be recorded. Additionally, patients will be asked to complete a daily calendar immediately after consuming their assigned treatments. Adherence to intervention refers to the extent to which trial participants’ behavior aligns with their assigned intervention. Adherence to the assigned treatments will be assessed through the use of a daily calendar during each phone call and by counting the returned packs at the end of the trial. Compliance will be calculated using the following formula: Compliance rate = (packs taken / packs prescribed) × 100. A compliance rate below 80% will be classified as poor compliance.

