### Outcomes {12}

This study will be conducted as a randomized double-blind placebo-controlled clinical trial to investigate the effects of inulin supplementation on clinical symptoms, inflammatory status, oxidative stress, intestinal permeability, mental health, and QOL in women with migraine. The primary outcome of this study is to evaluate the impact of inulin on the frequency of headaches in women diagnosed with migraines. In addition to this, the study will also focus on secondary outcomes, which include the assessment of serum levels of zonulin, Hs-CRP, total antioxidant capacity (TAC), total oxidant status (TOS), and NO. Furthermore, the mental health status, QOL, duration, and severity of migraine attacks will also be evaluated. The migraine symptoms, such as headache frequency, severity, and duration will be assessed by a neurologist. Participants will then be asked to complete questionnaires regarding the duration and frequency of the attacks during the intervention. The frequency of attacks will be recorded by the monthly incidence of headaches. The severity of pain will be assessed using a visual analogue scale (VAS) ranging from 0 to 10. Participants will be instructed to score 0 if they experience no pain and 10 if they suffer from agonizing pain. The study will measure the following parameters at the baseline and the end of the intervention: levels of zonulin, Hs-CRP, NO, TAC, and TOS, clinical symptoms, mental health status, and QOL. Blood samples will be collected from the patients both before and 12 weeks after the intervention with either inulin or placebo. These samples will be drawn in the morning (8–10 am) under fasting conditions. Following collection, serum will be separated from the blood samples through centrifugation and then aliquoted into 0.5-ml microtubes. The serum samples will subsequently be stored at − 70 °C in a freezer until further analysis.

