### Data management {19}

One of the researchers will oversee the coding, security, and storage of data. Data will be entered electronically at the participating site, and the forms will be securely stored on file. Furthermore, they will double-check data entry and values. If any patient reports adverse events, additional information will be gathered to determine whether to exclude them from the study. According to the Medical Ethics Committee Criteria, unblinding is permissible in this situation, allowing us to specify whether the patient received inulin or a placebo.

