### Statistical methods

#### Statistical methods for primary and secondary outcomes {20a}

Statistical analyses will be conducted using SPSS (version 21.0) software. A *P*-value < 0.05 will be considered statistically significant. The one-sample Kolmogorov–Smirnov test will be used to evaluate the normality of the distribution of data. Regarding missing values, the data analysis will be subjected to intention-to-treat (ITT) analysis. We will employ the multiple imputation approach to perform ITT. In order to compare the baseline value of qualitative and quantitative variables, the chi-square test and *t*-test will be used. Categorical variables will be expressed as number and percentage, while quantitative data will be presented as mean ± standard deviation. Between-group differences will be evaluated using a Mann–Whitney *U* test and independent *t*-test. Differences within the group will also be assessed with a Wilcoxon rank-sum test and paired *t*-test. To control for confounders, an analysis of covariance (ANCOVA) will be carried out.

The primary results of this study include the evaluation of clinical symptoms of patients, such as headache frequency, duration, and severity. The secondary results encompass the evaluation of the serum levels of zonulin, Hs-CRP, TAC, TOS, NO, mental health status, and QOL by questionnaire.

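### The rule eliminating data below 80% consumption conflicts with the promised ITT analysis, and stopping the supplement for a complication can trigger it

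*Protocol article*

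**What the plan says.** **Elimination rule.** The section Reason for eliminating the data consists of one line: "Consumption of less than 80% of inulin supplements by the patient". It names no analysis set. Section {11c} defines the measure ("Compliance will be calculated using the following formula: Compliance rate = (packs taken / packs prescribed", times 100) and labels a rate under 80% as poor compliance, but attaches no consequence to that label.

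**Analysis promise.** Section {20a} says "We will employ the multiple imputation approach to perform ITT". Section {21b} says dropouts stay in the analysis. Section {20c} says the ITT approach takes in the data of excluded patients and that missing values are multiply imputed.

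**Adverse events.** Under section {22}, for complications of supplementation "the intervention will be promptly discontinued, and the necessary medical measures will be taken". As a further step, "the ethical committee will determine whether to exclude the patient from the study", assign a code, or act in some other way. Section {19} says that after an adverse event "additional information will be gathered to determine whether to exclude them from the study", and section {11b} says "The investigator may withdraw patients from the trial to protect their safety".

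**Timing of the primary outcome.** Section {12} says "The study will measure the following parameters at the baseline and the end of the intervention", and clinical symptoms are on that list. Table 1 marks clinical features at week 1 and week 13 only. Sections {12} and {18a} also mention questionnaires on attack frequency covering the intervention period, with no time points of their own.

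**The concern.** An ITT analysis compares the groups as randomised. A rule that removes women according to how much supplement they took selects on something that happens after randomisation and may depend on the arm. If inulin causes gastrointestinal complaints that lead to stopping, the women removed from the inulin arm need not resemble those removed from the placebo arm, and the comparison loses the protection of randomisation.

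The article does not say which statement prevails. An analyst could follow the elimination rule and drop these women, follow the ITT sections and keep them, or blank their values and impute them. These are three different primary analyses, and the choice could be made after the data are seen.

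The adverse-event sections add a smaller issue. They allow a woman to be taken out of the study and not only off the supplement. If that ended her assessments, imputation would be the only way to include her. An analysis plan can overrule an elimination rule, but it cannot recover a week-13 value that nobody requested.

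**Working it through.** **1. The statements side by side**

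| Section | Effect on a woman below 80% |
|---|---|
| Reason for eliminating the data | Data eliminated, no analysis set named |
| {11c} | Labelled poor compliance, nothing more |
| {21b} | Kept in the analysis if she drops out |
| {20c} | Data included even if she is excluded |

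The first row conflicts with the last two for the same woman.

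**2. When stopping for a complication triggers the rule**

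- Packs prescribed: 1 per day × 7 × 12 = 84 (section {11a}).
- Threshold: 0.80 × 84 = 67.2 packs.
- 67/84 = 79.8%, below 80%. 68/84 = 81.0%, not below.

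A woman who takes every pack and is stopped at any point up to day 67 (week 10) is therefore caught, however well she complied until then.

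If packs prescribed means packs dispensed so far, taken here as 28, 56 and 84, she is caught when stopped after packs 1–22 (22/28 = 78.6%), 29–44 (44/56 = 78.6%) or 57–67 (67/84 = 79.8%). That is 22 + 16 + 11 = 49 of 84 possible stopping days.

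**3. Scale for the possible effect**

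The article gives no mean difference or SD, so its 40 per group cannot be reproduced. Solved backwards, with two-sided α = 0.05 (assumed two-sided) and 80% power:

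- detectable difference = (1.960 + 0.842) × √(2/40) = 0.626 SD
- standard error of the difference = √(2/40) = 0.224 SD

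**4. Illustrations (loss rates and differences are assumptions; the article gives none)**

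- One of the 40 inulin women returns to placebo level after stopping and is removed, or is imputed as if still on treatment. The shift is 1/40 × 0.626 = 0.016 SD, or 0.016/0.224 ≈ 7% of one standard error. With a true effect of zero, the shift is 1/40 × 0 = 0.
- A share of 10% of one arm is removed, and those women differ from the rest of the arm by 0.5 to 1.0 SD. The shift is 0.10 × 0.5 = 0.05 SD to 0.10 × 1.0 = 0.10 SD, which is 8% to 16% of 0.626 SD.
- Power at 0.626 SD falls from 80% to 78.0%, 75.7%, 73.3% or 70.7% if 5%, 10%, 15% or 20% of both arms are removed. It falls to 79.0%, 77.8% or 75.2% if only the inulin arm loses 5%, 10% or 20%.

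**The case against.** The strongest reply is that sections {21b} and {20c} speak directly to dropouts and excluded patients, while the elimination rule is one line under a short heading. A reader could let the explicit ITT statements prevail, and an analysis plan not shown may do so. That makes inclusion the likelier outcome. It does not remove the conflict, because the rule is stated without limit and never reconciled with ITT.

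The reply carries more weight on adverse events. Several stronger readings are tempting and not supported:

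- *A reader might infer that excluded women lose their week-13 outcome.* The text does not say assessments stop at exclusion. Section {18a} obtains clinical features from all participants, section {18b} schedules post-intervention visits, and {20c} counts on data from excluded patients. The inference rests on silence in a condensed article.
- *A reader might infer that no frequency data exist before week 13.* The questionnaires covering the intervention period could supply some and would help imputation, though Table 1 gives them no time point.
- *A reader might infer that every adverse event leads to exclusion.* In section {22} exclusion is one discretionary option among several. Section {21b} describes adverse events by grave examples such as death and disability; if that sense applies throughout, few women are affected.
- *A reader might infer that data are removed from the inulin arm only.* The rule does name only inulin, but the formula in {11c} applies to packs in both arms, so this may be loose wording. It still needs correcting, because the literal reading is one-sided.

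It is also fair to say that the likely bias is small and that nothing in the article allows it to be sized.

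**Conclusion.** The point holds in a limited form. The elimination rule and the ITT promise conflict as written. Because a complication stops the supplement, the rule reaches women with perfect earlier intake who stop at or before pack 67 of 84, so elimination can be related to treatment. The pack count follows from the article and assumes one pack daily with all 84 as the denominator; with packs dispensed so far as the denominator, the rule still covers 49 of 84 stopping days.

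How much the result would move cannot be derived. The illustrations suggest a small shift unless many women are removed, and in the return-to-placebo scenario there is none if inulin has no effect. The absence of an explicit request for outcomes after exclusion is a secondary matter that merits a clarifying sentence; it does not show that data will be lost. The rule should be corrected because it is a stated contradiction about the primary analysis and costs little to resolve.

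**What to change.** 1. In the section Reason for eliminating the data and in {20c}, state that the primary ITT analysis includes every randomised woman in her assigned group, whatever share of packs she took. Use the 80% threshold only to define a per-protocol sensitivity analysis, and word it for both inulin and placebo packs.
2. As a safeguard, state in {11b}, {19} and {22} that the default response to an adverse event in either arm is to stop the supplement, with the safety authority of the investigator and the ethics committee unchanged. State that the woman is still asked for her week-13 headache frequency, by telephone if needed, unless she withdraws consent for follow-up.

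The first change is an edit to the text and can be made at any time before analysis. The second needs a short amendment and one extra contact per discontinued woman; weekly calls already exist under {11a}. It helps only women whose week 13 is still ahead, and the article, which expects recruitment to end by March 22, 2024, does not show how many that is. Some women who stopped will decline, and their values would still be imputed.

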### Frequency and plans for auditing trial conduct {23}

This study will be conducted under the guidance of the Ethics Committee of Isfahan University of Medical Sciences. The Ethics Committee will oversee the quality, validity, and adherence to ethical standards by the researchers throughout the study period, with at least two monitoring sessions. A report will be submitted to the auditor every 3 months.

### Plans for communicating important protocol amendments to relevant parties (e.g., trial participants, ethical committees) {25}

Any changes to the protocol that may impact the implementation of the trial, such as modifications to study sample size, objectives, participants, or study procedures, must receive approval from the ethical committee of Isfahan University of Medical Sciences to be implemented. All changes will be reported in detail at https://irct.ir/.

### Dissemination plans {31a}

Final data and findings will be presented in official publications.

## Discussion

This study is, to the best of our knowledge, the first clinical trial evaluating the effects of inulin on migraine symptoms, mental health status, QOL, TOS, TAC, NO, zonulin, and Hs-CRP in women with migraines. Given the high prevalence of migraines and their impact on patients, it is imperative to explore novel and more effective therapeutic approaches for their treatment to alleviate pain and migraine attacks.

While the therapeutic effects of gut microbiota manipulation through the administration of probiotics/prebiotics have been discussed, there remains a dearth of information and unclear mechanisms regarding their potential to improve clinical outcomes in migraine patients. Moreover, the potential advantages of these biopharmaceuticals for individuals afflicted with migraines, who often endure headaches and a reduced quality of life, have not been extensively explored. This trial aims to address this critical research gap by investigating and comparing biomarkers of gut permeability, oxidative stress, and inflammation following inulin supplementation, as well as their subsequent impact on clinical outcomes among women with migraines. The innovative aspects of this clinical trial include (1) testing hypotheses related to inulin supplementation that involve a novel concept about the gut–brain axis, for which there is limited and incomplete data available in these subjects; (2) focusing on individuals at high risk for low quality of life, including those with migraines; and (3) conducting a 3-month follow-up with participants. Importantly, our findings could have a significant impact on clinical practice and public health by providing a simple and efficacious adjunctive approach for the prevention or amelioration of migraine headaches if our hypotheses are supported. The primary challenge of our study will be participant adhesion and retention. This challenge will be managed by the project coordinator who will have weekly contact with participants in which any concerns or issues will be immediately addressed. If these supplements are shown to be effective in the prevention or management of migraine headaches, they would represent a very attractive alternative or adjunctive therapy to current medications.

## Trial status

The protocol is version 3.0, September 17, 2023. Recruitment began August 21, 2023, and is anticipated to be completed by March 22, 2024.

## Abbreviations

ANCOVA: Analysis of covariance
BW: Body weight
BMI: Body mass index
CONSORT: Consolidated Standards of Reporting Trials
CH: Cluster headache
DASS-21: Depression, Anxiety, Stress Score
EF: Emotion Function
HIT-6: Headache impact test-6
Hs-CRP: High-sensitive C reactive protein
ICDH-3: International Classification of Headache Disorder-3
IRCT: Iranian Registry of Clinical trial
IPAQ: International Physical Activity Questionnaire
MIDAS: Migraine Disability Assessment Scale
MIHS: Migraine headache index score
MOH: Medication overuse headache
MSQ: Migraine Specific Quality of Life
NO: Nitric oxide
PA: Physical activity
RP: Role Preventive
RR: Role Restrictive
SPIRIT: Standard Protocol Items: Recommendations for Interventional Trials
SNRI: Serotonin–norepinephrine Reuptake Inhibitor
SD: Standard deviation
TTH: Tension-type headache
TCA: Tricyclic antidepressants
TeCA: Tetracyclic antidepressant
TAC: Total antioxidant capacity
TOS: Total oxidant status
TACs: Trigeminal autonomic cephalagia
VAS: Visual analog scale
WC: Waist circumference
